#### Literature Review on Interventions for Workplace Cyberbullying

There is limited literature available on interventions for workplace cyberbullying among TCM practitioners. Most of the available literature is limited to the identification of exploratory factors, measurement factors, and increasing trends of workplace cyberbullying. Funded by the Massey University Research Fund, D’Souza et al [23] discussed the issue of workplace cyberbullying in New Zealand; the study sample size was limited to 20 participants, but they predict an increase of workplace cyberbullying [23,24]. Vranjes et al [25] developed the inventory of cyberbullying acts at the workplace (ICA-W); the available results are preliminary items and build upon existing knowledge.

Moreover, the results of available literature are often generalized, noncontextual, and lack practical implications [25]. Another online self-report survey on workplace cyberbullying in New Zealand reports an increasing trend in workplace cyberbullying [26]; however, self-reported answers may be exaggerated and lead to an increase in survey bias. The studies of Farley [27], who had worked on the workplace cyberbullying measurement scale, are limited to methodological improvement in the measurement scale; these studies call for further exploratory studies. Other studies on the exploratory factors of workplace cyberbullying [27-29] lack coordination between theoretical and practical applications. The subjects of cyberbullying literature in Malaysia are limited mostly to adolescents and undergraduate students, and the focus is primarily on prevalence, the determination of exploratory factors, and descriptive studies [30-33]. The available studies are limited to examining the exploratory factors of workplace bullying [34].

Our studies will adopt the ERM in hospitals, and will adapt personalized mobile-based IT consumerization of the ERM in workplace cyberbullying among health care professionals as the intervention. A recent study also supports mobile phone– and internet-based interventions for treating depression [35]. Our study will be the first to use a personalized mobile mental health intervention for workplace cyberbullying for TCM practitioners.

#### Data Collection and Analysis

The recruitment of participants will follow the same procedure as was described for the exploratory study and prevalence study. The participant will be invited to join through a webinar to complete the questionnaire. Only the participants who completed Phase 2 will be asked to continue. The prototype will be given to them, and a brief training will be provided through a 30-minute webinar. Stage 3 participants will be limited to the Stage 2 completers in order to gauge the effectiveness of the Step 2 intervention program and whether the prototype is capable of reporting cyberbullying effectively. Thematic analysis will be done on the data yielded from the control and intervention groups. All the data of participants in this study will be password-protected and safe using Microsoft OneDrive.

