### Phase 2: Program Development

#### Objectives

The aim of Stage 2 is to develop the anticyberbullying intervention program. Past approaches have been ineffective because of a lack of consistency within the community. To achieve this objective, a quasi-experiment with a nonequivalent pretest–post-test control group design will be conducted for a duration of 1-1.5 years (Figure 5).

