#### Quasi-experiment with Nonequivalent Pretest–Post-test Control Group Design

The study design for this stage is quasi-experimental, in which the groups are nonrandomized into intervention and control groups and selected purposively. This study will be conducted in public hospitals and private hospitals located in Malaysia. All hospitals are eligible to participate. The selection of hospitals will be randomized for the implementation of the interventions. The randomization of hospitals will be performed by online statistical computing web programming to generate the randomization schedule [22]. The current methodology will help reduce selection bias in the study.

This intervention study will be conducted on TCM practitioners specifically. A baseline assessment will be done, in the intervention and control hospital, to measure the burden of bullying and its correlates using the CBQ and CBQ-S. This stage will begin after the investigation of prevalence and exploratory research. First, baseline information will be collected within 3 months, and then the intervention will be monitored twice after a regular period of 6 months in order to monitor the consistency of the intervention program.

The intervention program will be designed and finalized after (1) a systematic review of systematic reviews of previously published literature on bullying and the effectiveness of antibullying intervention programs; (2) the conducting of focus group discussions with TCM practitioners, patients, and other health care providers (to explore the perceptions, beliefs, and suggestions regarding bullying prevention programs); and (3) the conducting of a consultation workshop with all the stakeholders. The bullying intervention program (BIP) will pretest among 50 participants, which will include health care providers, TCM practitioners, and patients. The multicomponent hospital-based intervention strategy will be administered at 3 levels: (1) patients, (2) TCM practitioners, and (3) other health care providers. All the data of participants in this study will be password-protected and safe using Microsoft OneDrive. The recruitment of participants will follow the same procedure described for the exploratory study and prevalence study.

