### Phase 3: Electronic Anticyberbullying Monitoring System

#### Interface Design

An expert from each stakeholder group (TCM practitioners, other health care professionals, patients, and IT experts) will be involved in the interface design, information system design, and prototype testing. The system’s overall performance and satisfaction will be acquired through questionnaires (questionnaires are available upon request). The CBQ and CBQ-S will be used to determine the effectiveness of an intervention program using a prototype (post-test). The compilation of this research will be used to design the Personalized Mobile Mental Health Intervention (PMMH-I). The duration for stage 3 will be 6 months.

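### Restricting Phase 3 to Phase 2 completers in order to judge the Phase 2 programme selects on a post-intervention event and can bias the effectiveness estimate

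*Protocol article*

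**What the plan says.** Phase 2 is a quasi-experiment with a pretest–post-test control group design that "will be conducted for a duration of 1-1.5 years" (Phase 2, Objectives). On allocation, the design section says that "the groups are nonrandomized into intervention and control groups and selected purposively", and then also says that hospitals are randomized. It sets the first measurement, for which the instruments are the CBQ and CBQ-S: "A baseline assessment will be done, in the intervention and control hospital, to measure the burden of bullying and its correlates". After that, "the intervention will be monitored twice after a regular period of 6 months in order to monitor the consistency of the intervention program". No instrument is named for those two rounds.

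Phase 3 states the completer rule twice, both times under Data Collection and Analysis. First, "Only the participants who completed Phase 2 will be asked to continue". Then, with its purpose, "Stage 3 participants will be limited to the Stage 2 completers in order to gauge the effectiveness of the Step 2 intervention program". The same sentence gives a second purpose, which is to see whether the prototype can report cyberbullying. Under Interface Design, Phase 3 also holds the effectiveness post-test: "The CBQ and CBQ-S will be used to determine the effectiveness of an intervention program using a prototype (post-test"). The only analysis named for Phase 3 is qualitative: "Thematic analysis will be done on the data yielded from the control and intervention groups".

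The article gives no Phase 2 sample size, no expected dropout and no definition of a completer.

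**The concern.** This is a stated choice of evaluation population with a stated reason, so it is not a detail left to an analysis plan. Someone becomes a completer only after about a year or more in the study, with the intervention running. Whether they get there may depend on how much bullying they experience, how distressed they are, whether they leave the hospital, or what they think of the programme.

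Two separate problems can follow.

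- **Between groups.** If those who drop out differ from those who stay, and this selection differs between intervention and control hospitals, the two sets of completers are no longer comparable in the way the enrolled groups were. An inert programme could look helpful, or a useful one could look harmful.
- **Pre to post.** The Objective in the Abstract and the second research question are framed as pre and post effects. If people with high scores at follow-up are the ones who leave, completers show a fall from baseline that reflects who remained. This happens even when dropout is the same in both groups.

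Outcomes never collected from non-completers cannot be recovered by later analysis, so the rule matters before follow-up ends.

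**Working it through.** There is no stated figure to reproduce. The article gives no Phase 2 sample size, power, effect size or dropout. Its sample sizes of 1023 and 384 belong to the Phase 1 surveys and do not bear on this point. What can be done is to size the possible bias under declared assumptions.

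**From the article.** The evaluation population is Phase 2 completers, and there are two groups. The time over which dropout can occur is 3 + 2 × 6 = 15 months on the Methods schedule, or 4 + 2 × 4 = 12 months on the Results schedule.

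**Assumed.** True effect zero; follow-up CBQ standard normal, with higher scores worse; dropout fraction d; correlation r between follow-up CBQ and a latent tendency to drop out; correlation ρ = 0.6 between baseline and follow-up.

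**Step 1: mean among completers.** A person drops out when the latent tendency exceeds its (1 − d) quantile. The mean follow-up score in completers is then

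−r × k(d), with k(d) = φ(z₁₋d) / (1 − d).

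This gives k(0.1) = 0.195, k(0.2) = 0.350, k(0.3) = 0.497 and k(0.4) = 0.644.

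**Step 2: between-group bias.** Bias = −r_I × k(d_I) + r_C × k(d_C), in SD units, where I is intervention, C is control and a negative value is a false benefit.

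| Dropout, intervention / control | Selection | Bias, r = 0.3 | Bias, r = 0.5 |
|---|---|---|---|
| any | none (r = 0 in both) | 0 | 0 |
| equal | same r in both | 0 | 0 |
| 20% / 10% | same r in both | −0.05 | −0.08 |
| 30% / 10% | same r in both | −0.09 | −0.15 |
| 20% / 20% | intervention only | −0.11 | −0.18 |
| 40% / 20% | intervention only | −0.19 | −0.32 |

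For the last cell, 0.5 × 0.644 = 0.322. Exchanging the groups, or letting the better-off drop out, reverses each sign.

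**Step 3: a second dropout model.** In a simulation of 2 million records per arm, dropout was logistic in the follow-up score. Base dropout is the dropout probability at the mean score, and slope is the rise in log-odds of dropout per SD.

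| Base dropout | Slope, intervention / control | Unadjusted | Baseline-adjusted |
|---|---|---|---|
| 20% | 0.5 / 0 | −0.10 | −0.07 |
| 30% | 0.5 / 0 | −0.15 | −0.10 |
| 40% | 0.8 / 0 | −0.29 | −0.19 |
| 30% | 0.5 / 0.3 | −0.06 | −0.04 |
| 40% | 0.8 / 0.5 | −0.10 | about −0.06 |
| 30% | 0.5 / 0.5 | 0.00 | 0.00 |
| 40% | 0.8 / 0.8 | 0.00 | 0.00 |
| 30% | 0 / 0.5 | +0.15 | +0.10 |

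In the second row the observed dropout is about 31% against 30%, so similar completion percentages would not reveal the problem. Baseline adjustment removes only about a third of the bias (0.15 to 0.10).

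**Step 4: pre-post change.** If dropout depends on the follow-up score, the completers' baseline mean shifts by ρ times the follow-up shift. The false paired change is therefore −(1 − ρ) × r × k(d). At d = 0.2 and r = 0.3 this is 0.4 × 0.105 = 0.04 SD. At d = 0.4 and r = 0.5 it is 0.4 × 0.322 = 0.13 SD. The logistic model with the same slope in both groups gives 0.04, 0.06 and 0.12 SD for base dropout/slope of 20%/0.5, 30%/0.5 and 40%/0.8. The between-group bias is zero in those cases, but the pre-post distortion is not.

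**Step 5: after the fix.** If outcomes are obtained from everyone enrolled and analysed in the original group, this selection bias is zero by construction in the same scenarios.

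**The case against.** The strongest reply is that the completer rule governs who enters Phase 3 and does not say how Phase 2 data are analysed. Phase 2 is itself called a pretest–post-test control group design, and it has two later monitoring rounds that may yield outcome data on people who do not finish. The article nowhere says such data will be discarded. The Phase 3 post-test can also be read as a test of the prototype. A reader might therefore infer that effectiveness will be judged in completers and nowhere else. The documents do not support going that far. What stands is that the monitoring rounds have no named instrument and are described as checks on consistency, while the completer rule carries effectiveness as its own stated purpose.

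A second tempting reading is that the estimate will be biased, and in favour of the programme. That does not follow either. No dropout figures are given, and bullied staff may leave control hospitals just as readily. The larger false benefits above require outcome-related dropout in the intervention group only. Identical selection gives no between-group bias, and selection in the control group alone makes the programme look worse.

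Three further points are fair. Completers are a reasonable population for the prototype-reporting question, and the documents give no basis for saying that the rule inflates usability. The choice of statistical model and missing-data sensitivity analyses can be left to an analysis plan. The groups are also described as purposively selected, so baseline confounding could be as large as this bias. That last point does not make the completer rule harmless, because selection on completion is an additional problem.

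**Conclusion.** The concern holds in a limited form. The article ties a completer-only population to the aim of judging the Phase 2 programme and places its only named CBQ/CBQ-S post-test in that phase. This can bias the between-group estimate when dropout is related to the outcome and differs between groups. It can distort the pre-post change even when dropout is the same in both.

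Under assumed dropout of 20–40% and no true effect, the between-group bias lies between 0 and about 0.3 SD, in either direction. The false pre-post change is about 0.04 to 0.13 SD in the scenarios with 20–40% outcome-related dropout and a baseline–follow-up correlation of 0.6. Dropout rates, strength of selection and that correlation are all assumptions. The actual size and sign cannot be computed from the article.

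**What to change.** Reword Data Collection and Analysis in Phase 3 as follows.

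- Assess the effectiveness of the Phase 2 programme in all participants enrolled at Phase 2 baseline, by original hospital group, using all available CBQ/CBQ-S assessments.
- Send the online CBQ/CBQ-S post-test to participants who did not complete Phase 2 as well as to those who did.
- Report completion by group.
- Keep the restriction to completers only for testing whether the prototype can report cyberbullying.

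The cost is a wording change and extra invitations. Response among non-completers will be lower than among completers, so some missing outcomes will remain and the bias will be reduced but may not be removed. No stated sample size or power figure changes.

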### Research Questions

We aim to explore the following 4 research questions in this study: (1) What is the current workplace cyberbullying status among Traditional Chinese Medicine practitioners (TCM) in Malaysia? (2) What is the pre- and postefficacy of the Personalized Mobile Mental Health Intervention (PMMH-I) on the prevalence of measurable factors (ie, depression, anxiety, and stress) in workforce cyberbullying on TCM practitioners? (3) What are the moderating and mediating factors of workplace cyberbullying on TCM practitioners? (4) What is the technological feasibility of implementing the integrated PMMH-I as a component of routine hospital-based systems?

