### Study Plan

A hospital-based multimethod multi-analytic evidential approach is proposed, involving social and psychological health informatics. The project has been subdivided into 3 stages, starting with Phase 1, a prevalence study, followed by exploratory studies. Phase 2 consists of a quasi-experimental design, whereas the development of a prototype and their testing will be proposed in Phase 3. Flow diagrams for the research design are presented in Figures 2 and 3. A breakdown of our anticipated timeline for each phase of the study appears in Figure 4.

Each stage includes the use of quantitative and qualitative methods (mixed-method program), using SPSS (version 26.0; IBM Corp) and Stata (version 16.1; StataCorp) as tools for quantitative research, and NVivo (version 1.0; QSR International) and Atlas.ti (version 9.0.16; ATLAS.ti Scientific Software Development GmbH) for qualitative research.

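### The only analysis named for the control and intervention data is thematic analysis, which cannot estimate an effect on CBQ scores; a quantitative comparison using the planned baseline should be stated

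*Protocol article*

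**What the plan says.** - **Analysis.** Under Phase 3, Data Collection and Analysis: "Thematic analysis will be done on the data yielded from the control and intervention groups". The sentence is not restricted to interviews or free text. The same paragraph has participants complete a questionnaire and says that Stage 3 is limited to Stage 2 completers "in order to gauge the effectiveness of the Step 2 intervention program".
- **Outcome.** Under Phase 3, Interface Design: "The CBQ and CBQ-S will be used to determine the effectiveness of an intervention program using a prototype (post-test").
- **Question.** Research question 2 asks: "What is the pre- and postefficacy of the Personalized Mobile Mental Health Intervention (PMMH-I) on the prevalence of measurable factors", with depression, anxiety and stress given as the factors.
- **Design.** Phase 2, Objectives: "a quasi-experiment with a nonequivalent pretest–post-test control group design will be conducted".
- **Baseline and unit.** The quasi-experiment section says "A baseline assessment will be done, in the intervention and control hospital, to measure the burden of bullying and its correlates using the CBQ and" the CBQ-S, and also "The selection of hospitals will be randomized for the implementation of the interventions". No number of hospitals is given.
- **General statement on methods.** Study Plan, repeated in the Abstract: "Each stage includes the use of quantitative and qualitative methods (mixed-method program), using SPSS (version 26.0; IBM Corp) and Stata", with NVivo and Atlas.ti for the qualitative side. The only quantitative model named in the article is a structural equation model, and it belongs to the Phase 1 exploratory survey.

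**The concern.** The method named for the two-group data is of the wrong type for the outcome. Questionnaire scores in two groups call for a difference with an interval; thematic analysis yields themes. This is more than detail left to a fuller plan, because the article does name a method, and that method cannot answer the effectiveness question it is attached to.

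The stake is what happens when someone has to analyse the CBQ data. With no quantitative method fixed, the easy choice is a simple comparison of individuals. Two features of the design make that choice unsafe: the groups are declared nonequivalent, so baseline differences are to be expected, and the intervention is put in place by hospital, so practitioners within a hospital are not independent.

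**Working it through.** The article gives no alpha, power, SD, ICC, number of hospitals or sample size for the intervention-versus-control comparison, so there is no figure to reproduce. The two Phase 1 survey sizes (1023 and 384) were set by precision and do not bear on it.

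**1. Texts side by side**

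| Element | What the article states | Type |
|---|---|---|
| Effectiveness outcome | CBQ and CBQ-S | Questionnaire scores |
| Baseline | CBQ and CBQ-S in both groups | Questionnaire scores |
| Methods promised per stage | Quantitative and qualitative | Both |
| Analysis of control and intervention data | Thematic analysis | Qualitative only |

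The last row fits neither the outcome nor the general statement on methods.

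**2. What the baseline score is worth** (assumption: pre–post correlation ρ = 0.5–0.7, equal SD at both occasions). Variances are relative to post-test only:
- Baseline-adjusted: 1 − ρ² = 0.75 (ρ = 0.5) or 0.51 (ρ = 0.7). The reduction is 25% or 49%.
- Change score: 2(1 − ρ) = 1.00 or 0.60. Adjusted against change: (1 − ρ²) / [2(1 − ρ)] = (1 + ρ)/2 = 0.75 or 0.85. The reduction is 25% or 15%.

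**3. Why one estimate is not enough for nonequivalent groups** (assumption: baseline gap of 0.3 SD, no true effect, same ρ)

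| Estimate | Gap shrinks to ρ × 0.3 | Gap persists at 0.3 |
|---|---|---|
| Post-test only | 0.15 to 0.21 | 0.30 |
| Baseline-adjusted | 0 | (1 − ρ) × 0.3 = 0.15 to 0.09 |
| Change score | ρ × 0.3 − 0.3 = −0.15 to −0.09 | 0 |

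Entries are bias in SD units, for ρ = 0.5 and then 0.7. The adjusted estimate is unbiased in one case and the change score in the other. The article does not describe how the groups arise closely enough to say which case applies. Post-test only is biased in both.

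**4. Hospital** (assumptions: m = 20–50 practitioners per hospital, ICC = 0.02–0.05, normal approximation). Design effect DE = 1 + (m − 1) × ICC. The true error of a nominal 5% test that ignores hospital is 2[1 − Φ(1.96/√DE)].
- m = 20, ICC 0.02: DE = 1 + 19 × 0.02 = 1.38; 1.96/√1.38 = 1.67; error 9.5%.
- m = 50, ICC 0.05: DE = 1 + 49 × 0.05 = 3.45; 1.96/√3.45 = 1.06; error 29.1%.

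**5. Limit of any model.** The baseline sentence speaks of the intervention and control hospital in the singular. If that means one per arm, between-hospital variance cannot be estimated and the hospital difference is fully confounded with the intervention. Neither a hospital random effect nor a hospital-level permutation test would then help.

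**The case against.** The best defence is that the thematic-analysis sentence describes only the qualitative strand of Phase 3. The Study Plan promises both strands at each stage and names SPSS and Stata, so only the quantitative model would be unstated, which a condensed article may leave to a fuller plan. Part of this stands: a quantitative analysis may well be intended. A reader might infer that the study will produce no effect estimate at all, and the general statement on methods does not support that. It does not clear the sentence itself, which assigns thematic analysis to the group data without limit, in the section on analysis, next to a stated aim of gauging effectiveness.

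A reader might also infer that effectiveness will rest on a post-test-only comparison. The documents do not support this either. In Interface Design the term post-test marks a measurement occasion within a pretest–post-test design, and baseline scores are planned in both groups.

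It is also fair to object that the figures above describe a fallback the article does not propose, under assumed inputs. They show what is at risk if the method stays open; they do not measure the effect of using thematic analysis.

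Finally, a model of CBQ at two follow-ups would go beyond the text. The intervention is to be checked twice, but the instrument for those checks is not named.

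**Conclusion.** The point holds in a limited form. The only analysis the article names for the control and intervention data is one that cannot give a between-group effect on CBQ or CBQ-S, and it does not match the article's own promise of quantitative methods at each stage. This rests on the text alone and needs no assumption.

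The size is illustrative. Baseline adjustment would cut variance by 25–49% against post-test only and 15–25% against change scores if ρ is 0.5–0.7. Ignoring hospital would give a type I error of about 10–29% if there are 20–50 practitioners per hospital and the ICC is 0.02–0.05. None of these inputs is in the article. Whether hospital can be modelled at all depends on how many hospitals there are per arm, which is not stated.

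**What to change.** In Data Collection and Analysis:

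1. Restrict thematic analysis to focus-group and open-text data.
2. State that CBQ is compared between groups quantitatively, with CBQ-S supportive, using the baseline CBQ already planned in both groups. Say what role depression, anxiety and stress have, since research question 2 names them.
3. Report a baseline-adjusted estimate alongside a change-score (difference-in-differences) estimate, because the groups are nonequivalent. If the two disagree, the conclusion should say so.
4. State the number of hospitals per arm. With several, account for hospital and use a small-sample correction. With one, state that hospital and intervention effects cannot be separated and limit the conclusion accordingly.
5. Say whether CBQ is collected at the two monitoring occasions before any model uses them.

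The cost is mainly wording: the baseline CBQ and Stata are already planned. It adds a little analysis work, and intervals will be wider than in an analysis that ignores hospital.
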